### Trial design

The current study employs a Hybrid Type 3 design, evaluating the overall implementation while monitoring and collecting data on the clinical intervention's effects on important outcomes (9). Using a mixed-methods approach, the study integrates quantitative measurements and qualitative data collection across multiple stakeholder groups, including patients and healthcare staff. In addition, key structural and process parameters will be documented over time, and a health economic evaluation will be conducted. The study design is based on a modified stepped-wedge approach: The participating centers transition at different time points from a control condition—characterized by site-specific, non-harmonized PM practices—to the intervention condition, which reflects harmonized PM procedures. While this approach resembles the classical stepped-wedge design in its sequential rollout across sites, it deviates in one important aspect: The timing of the transition is not randomized. Instead, it is determined by administrative and organizational readiness. Specifically, a center enters the intervention group on the date documented in its certification form, which confirms that essential steps toward PM harmonization have been implemented. The certification criteria align with the standards set by the German Cancer Society (Deutsche Krebsgesellschaft) (8).

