### Sample size

The study aims to recruit a total of 4,807 patients, including 3,507 in the intervention group and 1,300 in the control group. The following assumptions underlie the sample size estimation: For nine newly established ZPMs (centers), two centers would be acceptable as dropouts. At least four existing centers in BW are considered unlikely to drop out, and seven newly initiated ZPMs serve as the basis for the sample size estimation. The new centers will contribute to controlling/intervening patients before/after initiation as ZPM, while the existing ZPM will only have intervention patients. This approach, inspired by the stepped-wedge design, has already been successfully used in several projects funded by the Innovation Fund (10). An average stay of 6 months in the control phase is assumed. It is estimated that each comprehensive cancer center (CCC) will have between 300 and 500 patients with PM, resulting conservatively in 1,300 control patients. This is compared with an estimated 3,500 ZPM patients from existing ZPM and those newly implemented during the study period. With these numbers, ignoring the cluster effect, differences of approximately 5% can be detected in the chi-squared test (Type I error 5% two-sided) with a power of >80% (exactly 86%) and differences of 7% with >90% (exactly 96%) power. Assuming a variance inflation due to cluster effects of 2, differences of 7% can still be detected with 85% power, and with very high cluster effects of 4 or 6, differences of 10% or 13% can be detected with 85% power.

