## Analysis and anticipated results

### Quantitative evaluation

The hierarchically organized endpoints described above (see Table 2) will be analyzed as binary variables (yes/no) while accounting for cluster effects from the individual centers using generalized estimating equations (GEE) in a logistic regression model (working correlation structure: exchangeable). The study arm (traditional procedure vs. standardized procedure according to the new form of care) will be coded as a binary variable, changing over time for centers newly included in the intervention condition. The Type I error rate will be set at 0.05 (two-sided). *P*-values for the secondary endpoints will be reported, but these should not be interpreted confirmatively. No corrections for multiple testing are necessary. Cluster effects will be addressed using GEE. In the primary analysis, we will use the independence estimation equation, and in a secondary analysis, we will use the exchangeable correlation structure within centers which allows for estimation of the cluster effect.

We expect the intervention to have a measurable impact on patient management as reflected in the primary outcome. Specifically, we anticipate the following effects across three levels of outcome assessment: Level 1, an increase in the frequency of indication-driven, standardized access to the MTB following implementation of the intervention; Level 2, a higher proportion of cases in which the recommendation for further diagnosis or therapy is modified as a result of MTB discussions under the harmonized approach; Level 3, an increase in the proportion of patients for whom the recommended changes in diagnostics or therapy are actually implemented in clinical practice. These analyses (Levels 1–3) will be additionally done with respect to the evidence level of the recommended therapies.

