These expected changes reflect the underlying hypothesis that harmonization and standardization of personalized oncology care will enhance the integration of MTBs into clinical workflows and improve outcomes for patients. However, we have to take into account that harmonization is a complex process and implementation is not done on a certain date. Thus, in secondary analyses, we will exclude patients in the last 3 and 5 months before certification from the control group, and in an additional secondary analysis, we will analyze the time trend in centers that were newly certified, correcting for the time trend in centers that had been certified already at the beginning of the project. AEs and SAEs are expected to remain within acceptable limits, indicating good tolerability. Additionally, we expect improvements in OS and PFS, among patients receiving targeted therapies based on molecular tumor profiling. These outcomes would support the clinical value of the intervention in routine care.

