### Methods for additional analyses (e.g., subgroup analyses)

#### Quantitative evaluation

Secondary analyses will be done adjusted for the characteristic “rare tumors yes/no,” as described in the inclusion criteria, as well as for the factor “urban/rural,” which arises from the regional structure of the participating CCCs. Planned subgroup analyses will be conducted for the individual CCCs, the type of tumors (rare: yes/no), and the demographic characteristic of urban vs. rural.

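### For Tiers 2 and 3 the primary model names study arm alone, so a calendar trend or a gap between established and new centres can pass for an effect of certification

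*Protocol article*

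**What the plan says.** All references are to the protocol article.

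- **Primary model** (Analysis and anticipated results, Quantitative evaluation). The endpoints are analysed as binary variables by logistic GEE, with centre as the cluster. On the regressor: "The study arm (traditional procedure vs. standardized procedure according to the new form of care) will be coded as a binary variable", switching over time in newly certified centres. The primary analysis uses independence equations. The same paragraph also names an exchangeable structure, but neither choice adds a time or centre term to the mean model.
- **Time trend** (same section). Among the secondary analyses: "in an additional secondary analysis, we will analyze the time trend in centers that were newly certified", corrected for the trend in centres certified from the start.
- **Case mix** (Methods for additional analyses, Quantitative evaluation). "Secondary analyses will be done adjusted for the characteristic" of rare tumour, and likewise for urban/rural.
- **Allocation** (Trial design). "The timing of the transition is not randomized"; it follows administrative and organisational readiness.
- **Centre roles** (Sample size). New centres supply control patients before certification and intervention patients after it, whereas "the existing ZPM will only have intervention patients". The target is a total of 4,807, "including 3,507 in the intervention group and 1,300 in the control group".

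**The concern.** A new centre's control patients always precede its intervention patients, and established centres have no control patients. An arm-only model with independence equations is a pooled, patient-weighted contrast. It sets later patients, together with all patients of the established centres, against early patients of the new centres. Clustering by centre changes the standard error but does not remove a trend or a centre difference from the estimate.

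The article itself gives grounds to expect both. Its introduction describes rapid advances in diagnostics and centres in Baden-Württemberg established by 2019. The section on adherence plans continuing improvement of documentation and the database, and the primary endpoint comes from forms completed by site staff. The Discussion expects the intervention to be modified during the study. Any of these could raise the Tier 2 or Tier 3 proportion without certification having an effect, and the confirmatory p-value would not tell them apart.

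**Working it through.** **1. The plan's own power.** Inputs from Sample size: 1,300 controls, 3,507 intervention patients, two-sided 5%, 5 points, no clustering. At a base rate of 50% (assumed; none is given):

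SE = √[0.25 × (1/1,300 + 1/3,507)] = 1.62 points; power = Φ(5/1.62 − 1.96) ≈ 87%.

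The chi-squared calculation gives 87.0%, or 86.3% with continuity correction, against the stated 86%. It reproduces, as a simple two-group comparison with no time or centre term.

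**2. Layout assumed for the bias.** From the article: seven new and four established centres, an average of 6 control months, and the arm sizes above. Assumed: 16 months of recruitment (registration in May 2023 to the stated end, 30 September 2024) and certification at months 3, 4, …, 9 (mean 6, mean square 40).

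- Accrual per new centre: 1,300/(7 × 6) = 30.95 a month.
- Intervention patients from new centres: 30.95 × (7 × 16 − 42) = 2,167. Established centres: 3,507 − 2,167 = 1,340, or 38%.
- Mean entry, controls: 40/(2 × 6) = 3.3 months.
- Mean entry, intervention: new centres (256 − 40)/(2 × 10) = 10.8, established centres 8.0; pooled (2,167 × 10.8 + 1,340 × 8.0)/3,507 = 9.7 months.
- Gap in calendar time: 6.4 months.

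**3. Spurious difference with no true effect.**

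From drift: drift per year × 6.4/12. From a centre gap: gap × 1,340/3,507.

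| Assumption | By formula | By simulation (base rate 40%) |
|---|---|---|
| Drift 2 points/year | 1.1 | – |
| Drift 5 points/year | 2.7 | 2.2 to 2.8 |
| Drift 10 points/year | 5.3 | 5.0 to 5.8 |
| Established centres 5 points better | 1.9 | 2.0 |
| Established centres 10 points better | 3.8 | 2.8 to 5.0 |
| Drift 5 and gap 5 | 4.6 | 4.5 |

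The simulation ranges cover 11 and 21 centres where both were run.

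Recruitment length shifts the balance. At 12 months the time gap is 3.68 months and the established-centre share 63%: drift of 5 gives 5 × 3.68/12 = 1.5 points, and a gap of 10 gives 6.3. At 20 months (9.25 months, 14%) the figures are 3.9 and 1.4.

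**4. Rejection rates with no true effect.** With 11 centres and neither drift nor gap, the arm-only model already rejects in about 8–11% of runs; that part is few-cluster inflation. At a drift of 5 points a year, rejection was 23% (11 centres) and 31% (21 centres) with a between-centre SD of 8 points, and 47% (11 centres) with no other centre variation. At 10 points a year it ranged from 45% to 91%.

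**5. Adding centre and calendar period.** Centre plus quarter terms bring the bias to 0.5 points or less. A version with centre indicators and linear time gave mean odds ratios of 0.99–1.02 and rejected in 3–6% of runs. With quarters and plain centre-clustered standard errors, 11 centres gave about 8–12%, so a small-sample correction is needed.

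**6. Precision after the change.** Variance of the arm coefficient relative to arm-only, base rate 50%, no residual clustering; power = Φ(d/(1.62 × √ratio) − 1.96).

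| Recruitment; certification months | Linear time: ratio; power for 5 / 7 / 10 points | Quarters: ratio; power for 5 / 7 / 10 points |
|---|---|---|
| 16; 3–9 | 2.37; 52 / 80 / 98% | 2.60; 48 / 76 / 97% |
| 16; 1–11 | 2.40; 51 / 80 / 98% | 2.43; 51 / 79 / 98% |
| 12; 3–9 | 2.58; 48 / 77 / 97% | 2.59; 48 / 77 / 97% |
| 20; 3–9 | 2.39; 51 / 80 / 98% | 3.47; 38 / 64 / 91% |

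With large centre variation (SD 8 points) and 11 centres the order reverses: the SD of the estimate was 2.4–2.7 points adjusted against 3.2–3.4 arm-only. With 21 centres arm-only was 2.1–2.3.

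**The case against.** **The article does not say that arm is the sole term.** This stands: it names only arm, in a condensed text. An unseen analysis plan might be thought to add time and centre, but the article places the trend correction and the case-mix terms in secondary analyses, which leaves little room for that.

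**The problem is disclosed and partly handled.** The abstract and Discussion acknowledge the lack of randomisation, and the planned trend-corrected analysis rests on the same idea as the fix below. That limits the harm but leaves the primary estimate and p-value unchanged. The other planned secondary analyses, which drop controls from the last 3 or 5 months before certification, address the blurred start date and make controls earlier still. In the layout above, dropping 3 months moves mean control entry to 13/(2 × 3) = 2.2 months and widens the time gap from 6.4 to about 7.6.

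**The magnitudes are assumed.** This also stands. Drift, centre gap, base rate, centre variation, recruitment length and certification spread are not in the article. At 2 points a year the bias is about 1 point.

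**Stronger readings the article does not support.** A reader might infer that the primary result will be a false positive; it could be, depending on a trend and gap nobody has stated. A reader might read all excess rejection as trend, but part is few-cluster inflation. A reader might extend the point and its remedy to Tier 1, but Table 2 defines Tier 1 as a number of patients and first MTB presentation is an inclusion criterion, so a logistic model of this kind does not apply there. A reader might suppose that disease severity is on file for adjustment; Table 3 lists diagnosis but no severity item, and severity appears only as a possible imputation predictor.

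**Conclusion.** The point holds for Tiers 2 and 3. As written, the primary contrast mixes certification with calendar trend and with differences between established and new centres. Assuming 16 months of recruitment, a 40% base rate and no true effect, the spurious difference is about 1 point at 2 points a year, 2–3 at 5, 5–6 at 10, and 3–5 if established centres are 10 points better. It could therefore reach the 5-point difference the trial is sized for. The direction follows the sign of the trend or gap; the examples assume both are positive. It would be wrong to infer that adjustment costs almost nothing: if centres vary little, variance rises about 2.4–3.5 fold. High power for a confounded contrast is nevertheless no reason to keep it as primary.

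**What to change.** Before outcomes are analysed, in a dated amendment:

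1. Make the primary Tier 2 and Tier 3 model arm + centre (fixed effects) + calendar period of T0, with rare tumour yes/no as an option. Keep the established centres in, so that they inform the period effects. Alternatively, promote the planned trend-corrected analysis to primary. Either way, state the assumption that established and new centres share the same underlying trend.
2. Use centre-clustered standard errors with a small-sample correction.
3. Keep the arm-only model as a sensitivity analysis.
4. Restate the power in Sample size for the adjusted model.

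The timing matters: recruitment ended on 30 September 2024, and the article expects data collection to finish by the end of November 2025 and results in January 2026.

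Cost: no extra patients or data, since centre and the day of first tumour board presentation are already part of the design. The price is precision. With little between-centre variation, power for 5 points is about 38–52% instead of the stated 86%; for 10 points it stays at about 90% or more.

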### Data collection and management

#### Quantitative evaluation

The primary endpoint contains three tiers. At Tier 1, the primary endpoint is the number of patients who receive an indication-driven, standardized access to the new form of care—personalized diagnostics and therapy—defined as access to the MTB. For this endpoint, a standardized data collection instrument will be developed to document both the original procedure and the newly implemented one, including the extent of the changes made (e.g., additional molecular diagnostics and therapy). The new procedure will be based on predefined, evidence-based criteria established by the ZPM network in BW. At Tier 2, it will be assessed for which patients the diagnostic process or diagnostic interpretation was significantly changed. Among this group, Tier 3 evaluates the proportion of patients for whom the changes ultimately led to treatment within the framework of personalized medicine. These changes may also include recommendations for genetic counseling, which—although not directly involving therapy or additional diagnostics—represent a modification in patient care.

Secondary clinical endpoints will be assessed continuously during the study: Adverse events (AEs) and serious adverse events (SAEs) will be recorded as they occur, and overall survival (OS) and progression-free survival (PFS) will be recorded every 6 months (T4–T8) until the end of the observation period, with a minimum follow-up of 6 months and an average follow-up of 12 months.

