### Methods in analysis to handle protocol non-adherence and any statistical methods to handle missing data

#### Quantitative evaluation

We differentiate between lack of adherence to the intervention and lack of adherence to the evaluation. Adherence to the intervention is part of the evaluation and will be analyzed but not adjusted in the analyses of outcomes. Non-adherence regarding the evaluation will be addressed by incorporating covariates that reflect relevant aspects of non-adherence into the regression models section. Additionally, separate analyses will be conducted for observational groups with varying levels of adherence. Any differences in outcomes between these groups, as well as the potential role of adherence as a predictor of treatment effectiveness, will be transparently analyzed and reported.

Assuming that missing data can be reasonably treated as missing at random, multiple imputation techniques will be employed to minimize the loss of valuable non-missing information that could occur with other methods, such as inadequate listwise deletion. We will use 500 imputation samples, study center, and center status (control vs. intervention) as predictors. Furthermore, we will consider diagnostic classes and measures of disease severity as potential predictors in the imputation model.

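### Tier 2 and Tier 3 proportions may rest on different patient mixes in the two arms, because the intervention changes MTB inclusion criteria and case mix is left out of the outcome model

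*Protocol article*

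**What the plan says.** **Selection is part of the intervention.** In the Protocol article, the section on project goals at the micro-, meso- and macro-levels puts MTB inclusion criteria first in the list of what the DNPM will standardise. Data collection and management, Quantitative evaluation, adds in its Tier 1 paragraph: "The new procedure will be based on predefined, evidence-based criteria established by the ZPM network in BW". Trial design describes control practice as specific to each site and not harmonised, and lets organisational readiness, not randomisation, set the transition date.

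**Study entry passes through the same gate.** Eligibility criteria require that the patient qualifies for the centre's MTB and is presented there for the first time.

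**The gate is expected to move.** For Level 1, Analysis and anticipated results, Quantitative evaluation, anticipates "an increase in the frequency of indication-driven, standardized access to the MTB following implementation of the intervention". Tier 2 is a proportion of patients with a changed strategy or recommendation (Table 2). Data collection and management then evaluates Tier 3 within the Tier 2 group.

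**What the model contains.** The logistic GEE is described with study arm as a binary variable, and no patient covariate is named. Methods for additional analyses says "Secondary analyses will be done adjusted for the characteristic" of rare tumour, and likewise for urban/rural. In the missing-data section, "we will consider diagnostic classes and measures of disease severity as potential predictors in the imputation model".

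**The concern.** If local criteria decided who reached the MTB before certification and harmonised criteria decide afterwards, the two arms' proportions are taken over different kinds of patient. Without randomisation, nothing in the design balances that mix. The existing Baden-Württemberg centres supply intervention patients only (Sample size), so their case mix enters one arm alone.

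If wider access brings in patients with fewer actionable findings, the Tier 2 proportion falls even when MTB decisions have improved. Success on Level 1 then counts against Level 2. If criteria become stricter, the proportion rises even when the board decides no differently for any given patient. Tier 3 inherits the problem because its denominator is the Tier 2 group.

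The other planned analyses do not address this. Dropping the last 3 or 5 months before certification, and comparing time trends with centres already certified, deal with gradual rollout and secular trend. The Discussion raises selection bias for the patient interviews only.

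**Working it through.** **Inputs from the document.** Sample size: "The study aims to recruit a total of 4,807 patients", "including 3,507 in the intervention group and 1,300 in the control group". Error rate: "The Type I error rate will be set at 0.05 (two-sided"). Stated power without clustering, for a difference of about 5 points and then 7: "with a power of >80% (exactly 86%) and differences of 7% with >90% (exactly 96%) power". With variance inflation 2, the stated power is 85% for 7 points.

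**Reproducing the plan's figures.** Power = Φ((d − 1.96·s0)/s1), where s0 is the pooled and s1 the unpooled standard error of the difference. Clustering is handled by dividing both arm sizes by the inflation factor. The document gives no base rate, so rates are centred on 50%.
- 5 points, no clustering (47.5% vs 52.5%): s0 = 0.01623, s1 = 0.01622, so Φ((0.05 − 0.03181)/0.01622) = Φ(1.12) = 86.9%. Stated: 86%.
- 7 points, inflation 2: 86.3%. Stated: 85%.

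Both agree closely, so 5 to 7 points is a fair yardstick. (A separate matter: 7 points without clustering gives 99.1%, not 96%; 6 points gives 95.9%.)

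**Effect of mix alone.** The document gives no Tier 2 rates or case-mix shares, so these are assumptions: p0 = 40% under control-type selection, pm = 20% in marginal patients, and no effect of the intervention within either type. The whole intervention arm is taken to have the changed mix.

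Widening adds marginal patients equal to a fraction w of the control group: p1 = (p0 + w·pm)/(1 + w).
- w = 0.1: 0.42/1.1 = 38.2%, shift −1.8 points
- w = 0.2: 0.44/1.2 = 36.7%, shift −3.3
- w = 0.3: 0.46/1.3 = 35.4%, shift −4.6

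Tightening removes marginal patients equal to a fraction t of the whole control group (not of the marginal patients): p1 = (p0 − t·pm)/(1 − t).
- t = 0.1: 0.38/0.9 = 42.2%, shift +2.2 points
- t = 0.2: 0.36/0.8 = 45.0%, shift +5.0
- t = 0.3: 0.34/0.7 = 48.6%, shift +8.6

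**Other base rates**, with pm at half of p0 and w or t from 0.1 to 0.3:
- p0 = 30%: −1.4 to −3.5 under widening, +1.7 to +6.4 under tightening.
- p0 = 50%: −2.3 to −5.8 under widening, +2.8 to +10.7 under tightening.

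**Smaller shifts are possible.** The false difference equals the rate gap between patient types times the shift in their share. A 10-point gap with a 10-point shift gives 1 point. A 20-point gap needs a 25-point shift to give 5.

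**Consequence under widening.** A true 7-point effect at inflation 2 has 86% power. Offset by 2, 3, 4 or 5 points of mix change, the power left is 59%, 41%, 26% or 14%.

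**The case against.** The strongest reply is that this is a Hybrid Type 3 study of a package, and the inclusion criteria belong to it. Better selection is then partly an intended result, and adjusting it away would estimate something narrower than the package effect. That stands. It is why the adjusted analysis belongs beside the arm-only contrast and should not replace it.

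Next, differing selection is implied, not documented. The eligibility list is the same for both arms, and the section on comparators says control patients meet the criteria for MTB inclusion. No section describes how local criteria differed before certification. The sentence on the new procedure could refer to diagnostics and therapy more than to admission. This limits the claim to a possible difference in mix. It does not remove it, because the comparator section does not say whose criteria controls meet, and harmonised criteria before harmonisation would not fit the stated control condition.

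A reader might infer that the design will produce a false success on Tier 2. At 1,300 vs 3,507, a mix-driven rise from 40% to 45% would be significant 88% of the time without clustering and 59% at inflation 2. That figure arises only under tightening. The objectives and Level 1 expect access to increase, which works against a Tier 2 success. Only the aim of preventing over-provision points the other way.

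A reader might also infer that selection switches on the certification date. The plan itself calls implementation gradual, so the 3- and 5-month exclusions may sharpen the contrast, but they do not make the mix comparable.

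Finally, a fuller covariate list may sit in a SAP that is not shown. That is fair. The article nevertheless fixes the arm term, two secondary adjusters and an imputation role for diagnosis and severity. Its subgroup analyses by centre and rare tumour, and its analyses by evidence level, do not standardise the arm comparison.

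**Conclusion.** The point holds as a structural weakness. The intervention covers MTB inclusion criteria, study entry depends on each centre's MTB, allocation is not randomised, and the outcome model as stated has no case-mix term. The Tier 2 and Tier 3 contrasts can therefore mix a change in decisions with a change in patients. Under the assumed rates, the shift for Tier 2 runs from −4.6 to +8.6 points, comparable with the 5 to 7 points the study is sized for, but smaller shifts are equally compatible with the document. Neither size nor direction can be derived from it. Masking is the more likely direction given the plan's own expectation; mimicry is possible if criteria tighten. The documents do not support saying that a bias has occurred, or that the arm-only contrast is invalid as an estimate of the package effect.

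**What to change.** In Analysis and anticipated results, Quantitative evaluation, keep the arm-only contrast as the package effect and prespecify beside it:

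1. A logistic GEE for Tiers 2 and 3 adjusted for case mix at T0: diagnostic class, rare tumour, prior therapies, age and sex, plus severity if it was recorded.
2. Arm differences from that model, reported as proportions standardised to one common patient mix.
3. A statement that Levels 2 and 3 are interpreted together with the change in who was admitted, with T0 characteristics shown by arm.

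Optionally, add a sensitivity analysis restricted in both arms to patients who meet the harmonised criteria, where T0 data allow. It addresses tightening. It cannot recover patients never presented under narrower local rules.

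**Cost.** Recruitment is closed, so the remedy lies in the analysis. Table 3 lists diagnosis, socio-demographics and recent therapies at enrolment, so most covariates need no new data collection. Severity is not listed there and must be checked. The model gains a few parameters and a standardisation step. Selection on unrecorded characteristics remains and should be stated as a limitation.

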Structural and organizational setup of the ZPM and its networkDecision-making processes in MTBsIT systemsDocumentationQuality managementBased on data harmonization processes introduced within ZPM-BW, all CCCs in Germany will now be enabled to integrate their structures and processes into the emerging DNPM. In this project, the new processes and structures outlined above will be implemented at CCCs across Germany, establishing further ZPMs. By the end of the project's funded period, a nationwide, digitally interconnected, interoperable, and patient-centered network will be in place to translate PM into patient care (7). This will considerably increase the amount of data, utilize the experience of 13 top centers, and significantly improve the possibility of comprehensive care in personalized oncology. To exchange this data (e.g., demographic patient data, diagnoses, treatment courses, genetic and pathological phenotype, recommendations from the MTB, and follow-up on these recommendations, as well as outcome data), the DNPM is creating a nationwide data platform, the dnpm:DIP, to enable secure, pseudonymized sharing of phenotypic, genomic, and imaging data between centers. This decentralized system supports quality control by national health insurers and facilitates data-driven decision-making in MTBs and patient inclusion in molecularly stratified trials (7).

To guarantee a comparable quality of innovative and interdisciplinary care across all centers, the DNPM has set up a certification system for the ZPM in the DNPM with the German Cancer Society [Deutsche Krebsgesellschaft (DKG), OnkoZert] and thus serves as a blueprint for clinical implementation.

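### The only stated calendar-time correction takes its reference trend from centres always under the intervention, so any growth of effect in those centres is subtracted from the estimate

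*Protocol article*

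**What the plan says.** In the protocol article, Analysis and anticipated results (Quantitative evaluation), the primary model is a logistic GEE in which the study arm "will be coded as a binary variable, changing over time for centers newly included in the intervention condition". No calendar-time term is named. Under Trial design, "The timing of the transition is not randomized"; a centre crosses over when its certification is documented.

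The same analysis section adds two kinds of secondary analysis of the transition. In the first, "we will exclude patients in the last 3 and 5 months before certification from the control group". This deals with a blurred onset, not with secular trend. The second is the only stated correction for time. It follows the new centres over calendar time, "correcting for the time trend in centers that had been certified already at the beginning of the project".

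Sample size describes the reference centres: new centres supply patients before and after certification, "while the existing ZPM will only have intervention patients". On their number it says: "At least four existing centers in BW are considered unlikely to drop out".

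Three sections bear on whether the effect in those centres stays constant:
- Intervention description makes a digitally connected registry a macro-level core measure meant to improve treatment recommendations.
- The section on the qualitative component of the process evaluation anticipates that collaboration among the centres in the national network will enhance care delivery.
- The Discussion lists iterative modification of the intervention during the study as a challenge.

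**The concern.** A reference trend should show how outcomes would have moved without the intervention. Centres certified from the start cannot show that directly, because all their patients are treated. Their trend is the secular trend plus any change in the intervention's effect. Subtracting it isolates the effect of certification only under two conditions: the effect in those centres does not change during the study, and their secular trend matches that of the new centres.

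The article gives reasons to doubt the first condition, since a network that improves care would reach the existing centres too. The loss would then be largest where the macro-level aim succeeds best. Because crossover is not randomised and the primary model names no time term, readers will look to this analysis to separate effect from time. The staggered roll-out offers another contemporaneous reference, the new centres not yet certified, and the reference trend does not use it.

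**Working it through.** **The plan's own figure, for scale.** Sample size gives 86% power for a 5-point difference, ignoring clustering. With 1,300 against 3,500 patients and an assumed base rate of 0.50, I get 87.0%, or 86.3% with continuity correction. At variance inflation 2, 7 points gives 86.5% (85.4% corrected) against the stated 85%. Both reproduce. Neither is disputed; they show that 5 to 7 points is the range the plan cares about.

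**Step 1: what the correction removes.** On the probability scale, let s be the secular trend per year, g the yearly growth of effect in certified centres, and d the direct effect of certification. Let t0 and t1 be the mean calendar times before and after certification.
- New centres change by d + s(t1 − t0) + g·t1.
- Reference centres change by (s + g)(t1 − t0).
- The difference is d + g·t0.
- The full effect at t1 is d + g·t1, so g(t1 − t0) is removed, whatever s is.

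Assumptions: d = 7 points, t0 = 0.25 year, t1 = 1.0 year, so g × 0.75 is removed.

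| g (points/year) | Full effect | Corrected estimate | Removed |
|---|---|---|---|
| 0 | 7.0 | 7.0 | 0 |
| 2 | 9.0 | 7.5 | 1.5 |
| 5 | 12.0 | 8.25 | 3.75 |
| 7 | 14.0 | 8.75 | 5.25 |

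**Step 2: which alternative helps.** Assumed layout: 4 existing centres; 7 new centres certified one per month at months 3 to 9 (mean 6, as Sample size assumes); 18 months numbered 0 to 17; equal weight per centre-month; d = 7 and g = 5.
- True mean effect: treated centre-months have mean month 952/84 = 11.33, so 7 + 5 × 11.33/12 = 11.7.
- Planned correction: with weight x(18 − x)/18 for a centre certified at month x, the mean pre-certification month is 1274/476 = 2.68, so 7 + 5 × 2.68/12 = 8.1.
- Period and centre effects fitted to all centres: 8.5. This regains 0.4 of the 3.6 points lost, because the existing centres still largely determine the period effects.
- Period and centre effects fitted to new centres only, months 0 to 8: the regression weights give a mean of 26.889/4.889 = 5.5 months, so 7 + 5 × 5.5/12 = 9.3. The true mean effect in that window is 7 + 5 × (133/21)/12 = 9.6.

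**Step 3: early implementation.** Same layout, g = 0, with an assumed 3-point gain in the 3 months before certification; the truth is 7.0.
- Planned correction, no exclusion: 7 − 3 × 252/476 = 5.4.
- New centres only, months 0 to 8, no exclusion: 7 − 3 × 6.571/4.889 = 3.0.
- New centres only with the planned 3-month exclusion: 7.0, because the affected months are gone.

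The new-centre analysis is therefore the more fragile one unless the exclusion goes with it. In this layout the exclusion reduces control centre-months from 42 to 21 (3 months) or 10 (5 months).

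**The case against.** The strongest reply is that an always-treated reference is legitimate. Under a constant effect and parallel trends the planned correction is unbiased, as the g = 0 row shows. That stands. A reader might infer that the analysis is biased in every case; the documents do not support this. A plateau in the existing centres is a possibility that the article neither states nor excludes.

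The evidence for growing effects is also indirect. Background and rationale expects the network to be in place by the end of the funded period and speaks of data and experience ("This will considerably increase the amount of data, utilize the experience of 13 top centers"). The network gains in the health economic section concern efficiency and cost. No section forecasts rising Tier 2 or Tier 3 proportions in existing centres. This limits what can be said about size, but the constancy assumption remains unstated and sits badly with the article's expectations.

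Not-yet-certified centres are an imperfect reference as well: the article says harmonisation does not happen on one date. Step 3 confirms this, and also shows that the article's own exclusion deals with it when the early gain falls inside the excluded months.

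Two further inferences should be resisted. Pre-certification patients are not ignored: they enter the primary contrast and the new centres' own trend, and are absent only from the reference trend. Nor can a power loss be read off. An assumed 3-point subtraction would take 7 points to 4, and power from 86% to about 41% at a standard error of 0.0230, but that is the standard error of the unadjusted comparison of 1,300 with 3,507 patients at variance inflation 2, not that of this analysis.

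**Conclusion.** The point holds in a limited form. The only stated calendar-time correction relies on centres that are always treated, and it needs a constant effect in them and parallel secular trends. The article states neither assumption and gives reasons to doubt the first. Growth of effect in those centres is subtracted one for one over the interval compared: nothing at g = 0, and 1.5 to 5.25 points at an assumed 2 to 7 points per year over 0.75 year. The growth rates, the direct effect, the times and the layout are all assumptions; the documents give no size. Only a secondary analysis is concerned, and the primary estimate is unchanged by it. The addition is worth making because it is cheap and because this analysis carries the separation of effect from time.

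**What to change.** Add one secondary analysis: calendar-period and centre effects, newly certified centres only, limited to periods in which at least one of them is not yet certified. Repeat it with the already planned 3- and 5-month pre-certification exclusions. Report it beside the planned analysis, and state there that the planned version assumes a constant effect in the existing centres and parallel trends. Period effects estimated from all centres are not enough on their own.

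The cost is some wording and a few model terms. Intervals will be wider, the usable window shorter, and the effect will refer to that window only. The 5-month repeat may rest on very little overlap, so the number of control patients and centres per period should be shown. The result also depends on how far not-yet-certified centres are already exposed to the network. Recruitment is complete, so the addition should be fixed before outcomes are compared by arm, or else labelled as added later.
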